## Abstract

**Background:** Mental disorders are highly prevalent among university students. Distance-learning students are particularly burdened and have limited access to conventional university health services. Interventions for stress are sought after in distance learners and may help increase treatment coverage. Internet-based interventions have been shown to be effective in preventing and treating depression, but it remains unclear if interventions directed at academic stress also have this potential.

**Aim:** The trial presented here investigates the effectiveness of an Internet- and App-based stress intervention in distance-learning students with elevated levels of depression.

**Methods:** A sample of *N* = 200 students of a large German distance university with elevated levels of depression [Center for Epidemiological Studies’ Depression Scale (CES-D) ≥ 16] will be randomly assigned to either an Internet- and App-based stress management intervention group (IG) or a control group (CG) receiving an Internet-based psychoeducational program for academic stress. The IG consists of eight Internet-based sessions promoting stress management skills using cognitive–behavioral and problem-solving techniques. A mobile App will be employed to facilitate training transfer. Self-report data will be assessed at baseline (T0), post-treatment (T1; 7 weeks), and 3-month follow-up (T2). Potential moderators will be assessed at baseline. The primary outcome is depression (CES-D) post-treatment. Secondary outcomes include mental health outcomes, modifiable risk and protective factors, and academic outcomes. Data will be analyzed on an intention-to-treat principle along with sensitivity analyses to assess the robustness of findings. Additional health economic analyses will be conducted.

**Discussion:** Results will provide the basis to assess the acceptance and effectiveness of Internet-delivered stress interventions in distance-learning students with symptoms of depression.

**Ethics and dissemination:** The study has been reviewed and approved by the University of Erlangen-Nuremberg ethics committee (Erlangen, Germany; 33_17 Bc). Results of the study will be disseminated through peer-reviewed publications.

**Trial Registration:**
German Clinical Trial Registration (DRKS), identifier DRKS00011800

## Background

Previous research documents that mental disorders are highly prevalent in tertiary education students (1–4). Depressive disorders are particularly common, with 12-month prevalence estimates ranging from 4.5% to 18.5% (1, 2, 4). Mental illness in the college years is associated with a broad range of adverse personal and societal outcomes, including lower academic performance (5–7) and college retention (8, 9), as well as worse physical health (10), and role functioning (11,12) in later adulthood. Suicidality is strongly associated with mental health disorders (13) and highly prevalent among university students (14–16), making it the second largest cause of mortality in this population (17).

Compared to the general university student population, distance learners may be particularly at risk for suffering from a mental disorder. Distance-learning services are frequently used by individuals over 30, by employees attaining qualifications in addition to holding a job, or by parents (18, 19). This may result in a more complicated educational environment for affected individuals (19, 20). Results from a survey among 5,721 German distance learners indicate that this population, compared to on-site students, faces great strain due to having to meet the demands of multiple societal roles (20). Resulting mental health problems have been associated with worse academic attainment in distance learners (21).

There is evidence that the large majority of students suffering from mental disorders do not receive any treatment for their mental health problems (1). Attitudinal factors such as personal stigma (22) or preference to deal with poor mental health on one’s own (23) have been discussed as major barriers in help-seeking.

Internet-based interventions have gained increasing attention as an instrument to foster health care utilization in adults (24). In recent years, the potential of Internet-based interventions to address mental health issues among tertiary education students has also become increasingly evident (25, 26). Contents can be easily accessed through the Internet, and Internet-delivered programs provide high scalability (27–29). Implementing Internet-based interventions in distance-learning university settings could represent a particularly promising approach, as distance-learning students commonly do not have direct access to on-site student counseling services.

Inclination to use Internet-based services has been found to be greatest among students reporting high levels of perceived stress (30, 31). In a survey among distance-learning students, interventions for relaxation and stress management were the most sought after, with 66.9% and 54.8% indicating interest in participation (20). Previous research suggests that Internet-based interventions for stress are often used by students with clinically relevant levels of depression who did not seek help through traditional healthcare channels (32). Disseminating Internet-based stress interventions could therefore be a non-stigmatizing way to increase treatment coverage among students suffering from depressive symptoms.

It is well established that perceived stress is a common contributor to the development of depression (33) and negatively affects its clinical course (34, 35). Internet-based stress interventions not only have been shown to be effective in reducing perceived stress (27) but also have been found to show moderate to high effects on depressive symptoms [Cohen’s *d* = 0.52–0.95 (32, 36–38)] even in participants with clinically relevant levels of depression at baseline [*d* = 0.67–1.19 (32, 39)]. These effects are comparable to the efficacy of conventional types of psychotherapy for depression [*d* = 0.62–0.92 (40)]. Together, this suggests that Internet-based stress interventions could be an effective way to reduce depression. Internet-based interventions for depressive symptoms have proven their effectiveness in preventing (41, 42) and treating (43) depression. However, no prospective trial has yet examined if Internet-based interventions for academic stress also have this potential in students with elevated levels of depression. It is also largely unknown if such interventions can have an impact on students’ academic productivity and work impairment. In general, it is still unclear which characteristics explain the heterogeneity of effects in the prevention and treatment of depression (44, 45). A broad assessment of variables predictive of differential intervention outcomes, risk and protective factors associated with the onset and maintenance of depression, as well as theoretically derived variables within intervention studies has therefore been proposed to increase our understanding of effect modifiers underlying interventions for depression [(44, 46); for an overview of potential effect modifiers in the prevention and treatment of depression, see Refs. (46, 47)].

The goal of the present study is therefore to i) evaluate the effects of an Internet- and App-based stress intervention in distance-learning students with heightened levels of depression on mental health outcomes, modifiable risk and protective factors for mental health disorders, and functioning outcomes when compared to an active control group (CG) receiving an Internet-based psychoeducation program on stress management; ii) to investigate the moderators of potential treatment effects; iii) to assess the help-seeking intentions of study participants; and iv) to assess the interventions’ health economic benefits when implemented into routine care. We hypothesize the Internet- and App-based intervention group (IG) to be more efficacious when compared to the active CG receiving the psychoeducation program.

## Methods

### Study Design

We will conduct a two-armed randomized controlled trial (RCT) comprising two conditions: the IG, receiving an Internet-based intervention with feedback on demand (*StudiCare Fernstudierende*), and a waitlist CG receiving psychoeducation during the study phase, and access to *StudiCare Fernstudierende* after the study. Both study conditions will have full access to treatment as usual (TAU; including general practitioner visits, counseling services, psychotherapeutic and psychiatric treatment or other forms of primary, secondary, or tertiary care). The trial will be conducted and reported in accordance to the Consolidated Standards for Reporting Trials (CONSORT) Statement (48) and the Guidelines for Executing and Reporting Research on Internet Interventions (49). We aim to communicate results of this study through peer-reviewed publications in psychiatric or eHealth journals. In addition, code scripts for all statistical analyses will be made publicly available on an Open Science Framework repository (OSF; www.osf.io).

Assessments will take place at baseline (T0), post-treatment (T1; 7 weeks after randomization), and 3-month follow-up (T2; see **Figure 1** for a detailed overview of assessment points). Self-report data are collected using a secure online-based assessment system (Advanced Encryption Standard, 256-bit encryption). All procedures involved in the study are consistent with the generally accepted standards of ethical practice. The study was approved by the University of Erlangen-Nuremberg ethics committee (Erlangen, Germany; 33_17 Bc). The trial is registered in the German clinical trials register (DRKS00011800). The trial proceedings presented here are reported in accordance to the Standard Protocol Items: Recommendations for Intervention Trials (SPIRIT) statement (50). The populated SPIRIT checklist can be found in **Table S1 in the Supplementary Material**. The SPIRIT figure is presented in **Figure S1 in the Supplementary Material**.

**Figure 1 f1:**
[figure not shown]
Study flow.

### Participants

Students will be included if they i) experience elevated levels of depression measured by a score of ≥16 on the German version of the Center for Epidemiological Studies’ Depression Scale (CES-D) 20-item version [ADS (51), indicating subthreshold to full-blown symptoms of depression during the last 2 weeks], are enrolled in a ii) bachelor’s or iii) master’s degree program at a large German distance-learning tertiary education facility (*FernUniversität in Hagen*) by the beginning of the intervention, iv) are at least 18 years old, v) have Internet access, vi) declare willingness to provide self-report data at all three assessment points, and vii) give informed consent. Exclusion criteria will be i) self-reported dissociative symptoms or psychosis, currently or in the past, or ii) a considerable risk for suicide as indicated by a score higher than 1 on item 9 of the German version of the Beck Depression Inventory [BDI-II (52); “I feel I would be better off dead” or “I would kill myself if I had the chance”]. Students will not receive monetary compensation for participating in the intervention.

### Recruitment

Participants will be recruited in German-speaking countries (Germany, Austria, Switzerland) *via* social media advertisement, university press reports, and information letters distributed through the distance-learning universities’ mailing list. Potential participants will be able to declare interest for partaking in the study by filling out an online registration form on a website created for the intervention that also contains further information about the intervention and eligibility criteria.

### Assessment of Eligibility and Randomization

Individuals who declare their interest in participating in the study will receive an online letter with detailed information about the study procedure and will be asked to provide an e-mail address as well as a first and last name (which may be pseudonyms) for their intervention platform profile. Applicants will be informed that withdrawal from the study is possible at any time without negative consequences and that all collected case data can be deleted on request during the study. Participants will then be asked to fill out the online screening questionnaire.

Individuals fulfilling all inclusion and none of the exclusion criteria will be asked to fill out an informed consent form. Individuals who provide us with their informed consent will be invited to fill out the baseline assessment, which will take approximately 30 min to complete. Subsequently, individuals will be randomly allocated to either the IG or the CG. Randomization will take place at a ratio of 1:1 and a block size of 2 using an automated computer-based random integer generator (*Randlist*, Datinf GmbH, Tübingen, Germany) and will be performed by a researcher who is not involved in the study. Participants will not be blinded to study conditions, yet during the randomization process, the allocation will be concealed from participants, researchers involved in recruitment, and e-coaches.

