### Guidance

In order to support participants in adhering to the intervention while minimizing human capital costs, we will apply an adherence-focused guidance concept with personalized feedback on demand [for a detailed description of an application, see Refs. (38, 73, 74)]. The supportive accountability model suggests that the adherence and effectiveness of Internet-based interventions are enhanced by providing a minimum of human support by a professional seen as benevolent and competent by participants (75, 76). The guidance concept for this study was developed in line with these core elements.

Guidance for the IG will be performed by a specially trained student in a master’s program in psychology and consists of three parts: i) monitoring adherence to the intervention, ii) sending standardized motivational messages after every module, and iii) providing feedback on demand. Adherence monitoring involves personal reminders for participants who had not completed a session in the designated timeframe (7 days). Standardized motivational messages tailored to each session will be sent when participants completed one of the main modules, summarizing the content of the previous module and motivating trainees to stay engaged. Feedback on demand will be provided through the internal messaging system of the training platform, which participants may use whenever individualized content feedback is needed. Participants will then receive feedback within 48 h. If requested, participants in the IG will be able to receive automatic messages containing short, motivational prompts *via* SMS.

Participants in the active CG will receive parts (i) and (ii), but will not receive feedback on demand.

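### A fixed block size of 2 in an open, unstratified trial makes every second allocation predictable to staff who learn the one before, which weakens the claimed concealment

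*Protocol article*

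**What the plan says.** All of the following is from the protocol article.

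- *Assessment of Eligibility and Randomization* fixes the scheme: "Randomization will take place at a ratio of 1:1 and a block size of 2". The list comes from a software random integer generator. No stratification factor or second block size is mentioned.
- The same section says that randomisation "will be performed by a researcher who is not involved in the study", that "Participants will not be blinded to study conditions", and that "during the randomization process, the allocation will be concealed from participants, researchers involved in recruitment, and e-coaches".
- It also sets the order of events: online screening, consent, baseline questionnaire, then allocation ("Individuals who provide us with their informed consent will be invited to fill out the baseline assessment").
- *Guidance* makes the arms distinguishable to whoever delivers support: "Participants in the active CG will receive parts (i) and (ii), but will not receive feedback on demand". Tables 1 and 2 show different module content in the two arms.
- *Participants* sets a numeric self-report entry rule: students must "experience elevated levels of depression measured by a score of ≥16" on the CES-D.

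**The concern.** With one fixed block size of 2, each block is either IG–CG or CG–IG. Once the first arm of a pair is known, the second carries no randomness. An uninvolved randomiser protects the list, but cannot protect the second allocation of a pair once the first has become visible, and in an open trial allocations do become visible to those who deliver the programmes.

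The concealment sentence covers only the period of the randomisation itself. It does not say that recruiters or e-coaches remain unaware of earlier allocations, or that the block size is kept from them. Because the sentence names both groups, the protocol itself treats their knowledge as relevant.

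At stake is selection bias. If someone who can foresee the next arm also affects when, or in what order, cases reach the randomiser, the arms may differ in characteristics other than the baseline score. The ANCOVA in *Statistical Analyses* adjusts for the baseline value of the outcome, but not for features such as motivation, which the *Discussion* names as a selection issue in recruitment. Nothing in the design appears to require blocks this small.

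**Working it through.** **Inputs.** 1:1 ratio and block size 2 (*Assessment of Eligibility and Randomization*); N = 200, d = 0.40, 80% power, two-sided alpha 0.05 (*Sample Size*). The article gives no figure for predictability.

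**1. The plan's own figure.** n per arm = 2(1.96 + 0.8416)² / 0.40² = 98.1 by the normal approximation, and 99 after rounding up. N = 198, which agrees with the planned 200. Power at 100 per arm is 80.7% (normal) or 80.4% (t-test). The block size does not affect this.

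**2. Predictability of permuted blocks.** Take an observer who knows the block size, the order and all earlier allocations, and always guesses the arm with more places left. For blocks of size 2b:

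- fraction known with certainty = 1/(b + 1)
- expected correct-guess rate = [b + (4^b / C(2b, b) − 1)/2] / (2b)

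For b = 1: 1/2 = 50%, and [1 + (4/2 − 1)/2]/2 = 1.5/2 = 75%.

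| Scheme | Certain in advance | Of 200 | Correct guesses |
|---|---|---|---|
| Block 2 (protocol) | 50.0% | 100 | 75.0% (150) |
| Block 4 | 33.3% | about 67 | 70.8% |
| Block 6 | 25.0% | 50 | 68.3% |
| Block 8 | 20.0% | 40 | 66.6% |
| Simple randomisation | 0% | 0 | 50.0% |

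Block 2 is the most predictable permuted-block design at 1:1. Exact enumeration of the blocks gives the same values as the formulas.

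**3. Randomly mixed blocks of 4, 6 and 8, equally likely.** Weighting by block length, the guess rate is (4 × 0.7083 + 6 × 0.6833 + 8 × 0.6661)/18 = 12.26/18 = 68.1%. Guessing the arm that is behind does not require the block size, so mixing does not bring this below fixed blocks of 8. What falls is certainty. Even if every size leaked, the certain fraction would be (4/3 + 6/4 + 8/5)/18 = 4.43/18 = 24.6%, and it is lower for an observer who does not know the sizes.

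**4. Cost of simple randomisation.** The SD of one arm's size is √(200 × 0.25) = 7.1. A one-SD split of 93/107 is equivalent to 2 × 93 × 107/200 = 99.5 per arm. Power is then Φ(0.40 × √(99.5/2) − 1.96) = Φ(0.86) = 80.5%, against 80.7% at 100 per arm.

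**5. Sensitivity of a retrospective check.** There are 100 second-in-pair participants, about 50 per arm. The difference detectable with 80% power is (1.96 + 0.8416) × √(2/50) = 0.56 by the normal approximation, and about 0.57 with the t distribution.

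**The case against.** A reader might infer that concealment is undone, or that it cannot be kept for half the sample. The document does not support that.

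- Prediction needs one person who knows the block size, the order and the previous allocation, and who can also affect enrolment. The article does not say that recruiters see earlier allocations, or that e-coaches recruit. It does not rule either out. The 50% and 75% are therefore upper bounds for a fully informed observer, not expected rates.
- Participants do not see one another's allocations, so concealment from them stands. The first place in each pair remains 50/50.
- Candidates register and screen online, eligibility rests on self-report cutoffs, and consent and baseline are complete before allocation. This leaves staff little discretion over who enters.

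All of this stands, and it limits the concern to the timing of contact and the order in which completed cases are passed to the randomiser.

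Two further inferences should also be resisted. The unblinded self-report outcome does not make selection bias worse in the sense that a blinded measure would have offset it: blinded assessment limits detection bias and does not change who enters each arm. Nor do mixed blocks of 4, 6 and 8 beat fixed blocks of 8 on the guess rate (68.1% against 66.6%); their advantage is in the fraction known with certainty.

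**Conclusion.** The point holds in a limited form. A fixed block size of 2, in an open 1:1 trial with no stratification stated, makes up to 100 of 200 allocations certain and up to 75% guessable for staff who know the block size, the order and the previous allocation. The concealment statement does not address this, so concealment from recruiters and e-coaches is weaker than the text suggests.

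The arithmetic is exact. Whether any bias follows depends on what staff knew and on their influence over processing order, neither of which the article states. Sample size and nominal power are unaffected. The change is worth making because the small block brings almost no benefit at N = 200 and the alternative is nearly free.

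**What to change.** **Allocations not yet made.** Generate a new list by one of two routes:

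- simple randomisation (0% certain, 50% guess rate); or
- randomly varying blocks, for example 4, 6 and 8, with the sizes withheld from recruiters and e-coaches (guess rate about 68%, with far fewer allocations known with certainty).

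State in the protocol that block sizes and earlier allocations are not disclosed to those who recruit.

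**Allocations already made.** *Trial Status* gives a recruitment start in April 2017 and last follow-up by March 2019. With T2 at three months after randomisation, allocation would end around December 2018, so few or none may remain and this part may carry most of the weight. Report who knew the block size and earlier allocations, and when. Compare baseline characteristics between arms among second-in-pair participants: CES-D, and also variables that the ANCOVA does not adjust for, such as treatment expectancy (CEQ). Present this as a check of limited sensitivity.

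**Cost.** A new list, a sentence or two in the protocol, and one descriptive table from data already collected. The downside is a small final imbalance in arm sizes, with negligible loss of power.

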### Participant Safety

A standardized operating procedure will be followed in case individuals are defined as showing an elevated risk for suicide. During the screening process, individuals will be excluded from the study and given detailed information about emergency contact numbers and treatment options for depression based on the German S3-guidelines for unipolar depression (53). Individuals will also be asked to see their physician or a psychiatrist as soon as possible to initiate psychiatric or psychotherapeutic treatment. The same procedure will be followed if participants who were included in the trial show symptoms of suicidality throughout the study phase (i.e., by mentioning symptoms of suicidality when contacting their designated eCoach, or when responses to intervention content hint at potential suicidal ideation). These participants will be contacted additionally to determine the severity of suicidal symptoms and discuss next treatment steps. This process will be supervised by an experienced clinician at the first author’s host institution.

